## Abstract

**Background:**

The exploration of interventions to delay aging is an emerging topic that promotes healthy aging. The multidomain intervention has the potential to be applied in the field of aging because it concentrates on the functional ability of older adults. There is currently no literature reporting on a multidomain intervention involving cognition, exercise and nutrition for delaying aging.

**Methods:**

The Multidomain Intervention for Delaying Aging in Community-dwelling Older Adults (MIDA) is a Zelen-design randomized controlled trial with a 6-month intervention duration. The multidomain intervention comprises cognitive training, exercise training, and nutritional guidance, delivered through both group sessions and individual family interventions. A total of 248 participants aged 60 to 85 years will be randomized to the intervention group or control group and followed up for 12 months. The primary outcome is the change in epigenetic age acceleration and pace of aging following the multidomain intervention. The secondary outcomes are the changes in frailty score and intrinsic capacity Z-score. Other outcomes include physical functions, body composition, aging biomarkers, inflammatory markers, haematology and biochemistry parameters, and lifestyle factors.

**Conclusions:**

This study will explore the effects of the multidomain intervention on delaying aging in community-dwelling older adults. We aim to introduce a new approach to delaying aging and offer a practical multidomain intervention strategy for healthcare institutions.

## Introduction

In recent years, studies on aging interventions have mainly focused on singular approaches such as anti-aging drugs, calorie restriction diets, and exercise interventions [1]. However, contemporary geriatricians advocate for a holistic intervention model that integrates multiple intervention strategies. This transformation is rooted in the understanding that promoting health is a person-centered process that encompasses the entire organism, rather than single disease or specific organ functions [2]. Older populations often have multiple risk factors and complex health conditions, making single-type interventions insufficient to address all health issues. The multidomain approach to aging intervention not only allows each intervention component to serve different health goals but also results in better delayed aging effects compared to single-type interventions [2,3].

Multidomain intervention, as a concept combining two or more intervention modes, has currently gained widespread attention in the field of geriatric medicine [4]. Aging is a multifactorial process involving declines in physical, cognitive, and nutritional aspects. Therefore, in our multidomain intervention strategies, we concentrate on three intervention methods: cognitive intervention, exercise intervention, and nutritional intervention. As they are used as single-type interventions, they can respectively bring about positive improvements in specific diseases or geriatric syndromes among the older population. Firstly, exercise intervention can not only prevent cardiovascular diseases, diabetes, and obesity, but also improve muscle function, mental health, and quality of life, and reduce all-cause mortality [5]. Meanwhile, a healthy diet pattern can not only slow down the age-related decline in physical function but also reduce the occurrence of adverse events [6]. In addition, cognitive training is an intervention measure with high operability and no obvious adverse reactions. It can promote cognitive ability and daily living ability for older adults at any stage of cognitive impairment or with normal cognitive levels [7,8]. The Integrated Care for Older People (ICOPE) guidelines, released by the World Health Organization [9], has proposed recommendations for exercise, nutrition, and cognitive interventions for older adults. Multidomain intervention by simultaneously targeting excercise, cognitive and nutritional domains has the potential to synergistically enhance functional ability and slow down age-related declines.

Several multidomain intervention studies have utilized a combination form of cognitive, exercise, and nutritional interventions. For instance, the Finnish Geriatric Intervention Study to Prevent Cognitive Impairment and Disability (FINGER) included older adults at risk of cognitive decline, indicating that multidomain intervention could reduce the occurrence of cognitive impairment and cardiovascular events [10,11]. The Frailty Intervention Trial (FIT) in Singapore developed by Tze Pin Ng et al. demonstrated a 6-month multidomain intervention significantly decreased the severity of frailty and sarcopenia in pre-frail and frail older adults [12,13]. Additionally, the Taiwan Health promotion Intervention Study for Community Elders (THISCE) revealed improvements in physical and cognitive function, as well as addressing malnutrition and depression in pre-frail and frail older adults [14]. However, the Multidomain Alzheimer Preventive Trial (MAPT) in France, which targeted older adults with subjective memory impairment, did not show a significant impact of multidomain intervention on cognitive function, muscle strength, or intrinsic capacity (IC) [15–17]. While the combination of exercise, cognitive, and nutritional interventions has been employed in studies addressing frailty, sarcopenia, depression, and cognitive impairment among common geriatric syndromes, this multidomain intervention strategy has not been explored in the field of aging with biological age as the primary outcome. Therefore, this study aims to implement cognitive, exercise, and nutritional interventions as a practical approach for multidomain intervention in the clinical practice of aging research.

The epigenetic clock is constructed from DNA methylation modifications at cytosine-phosphate-guanine (CpG) sites in the human genome. It uses mathematical algorithms to aggregate CpG sites associated with age, enabling the estimation of an individual’s epigenetic age [18]. Epigenetic age represents a biological age derived from methylation data and can predict mortality and age-related diseases such as cardiovascular diseases, Alzheimer’s disease, and cancer [19]. Given the potential reversibility of epigenetic age, an increasing number of aging studies are exploring interventions aimed at decelerating epigenetic aging [20]. Accordingly, this study will use epigenetic clocks as the primary outcome measure for aging.

The outcome measures characterizing aging are not singular. Authoritative scholars recommend the incorporation of diverse aging-related indicators as alternative aging endpoints in the same study to enhance the understanding of aging [21]. We include frailty and IC as secondary outcomes for aging in this study. IC refers to the overall status of an individual’s physical and mental abilities across five domains: locomotor, vitality (nutrition), cognitive, psychological, and sensory functions [22]. The introduction of IC signals a shift in focus within healthy aging towards keeping optimal physiological reserves in older adults [23]. Frailty and IC seem like two sides of one coin. Frailty, indicative of the accumulation of physical deficits with age, represents a negative state, while IC signifies a positive state reflecting functional reserves. IC not only complements the health information provided by frailty, but also serves as a dynamic indicator that can be monitored longitudinally throughout the lifespan [24]. Interventions targeting IC are currently in the early stages of research and are anticipated to become a focal point in the geriatric medicine [25].

In summary, this study will develop a multidomain intervention program tailored for community-dwelling older adults, integrating cognitive, exercise, and nutritional interventions. Epigenetic age accleration and pace of aging will be used as the primary outcome measure, while frailty and IC will serve as secondary outcome measures to characterize aging. Subsequently, a 6-month multidomain intervention study will be conducted to investigate the effects of the intervention on delaying aging in community-dwelling older adults.

## Methods

### Study design

The MIDA study employs a Zelen-design for randomized controlled trial [26], which combines elements of an observational study with post-randomization informed consent and a randomized controlled trial. The cognitive, exercise, and nutritional interventions in the multidomain approach require close participant cooperation under the guidance of healthcare professionals, especially in individual home-based interventions. Maintaining blinding of assigned groups to participants poses a challenge. Furthermore, traditional randomization methods may result in decreased participant compliance, increased attrition rates, and higher demands for sample size and funding. Therefore, the Zelen-design is suitable for randomized controlled trial where maintaining blinding is difficult. It allows participants to provide further informed consent based on individual circumstances post-randomization. The Zelen-design can enhance compliance with follow-up procedures, align with real-world clinical settings, and better reflect clinical practice realities.

This study employed the Proactive Health Management Platform for Older Adults (SilverHealth Pro Platform, SPP), which was developed by the Fujian Provincial Center for Geriatrics. This study protocol has been approved by the Ethics Committee of Fujian Provincial Hospital (K2023-04-039) and registered with the Chinese Clinical Trial Registry (ChiCTR2300072010). The trial protocol is in accordance with the CONSORT guidelines [27].

### Participants and recruitment

The trial will be conducted at the Fujian Provincial Center for Geriatrics. Recruitment will be conducted through printed posters in outpatient departments of Fujian Provincial Hospital and community health service centers, as well as electronic poster dissemination *via* WeChat groups and social media accounts. Interested participants will register by contacting the recruitment staff. Physicians from the Fujian Provincial Center for Geriatrics will carry out the screening according to the inclusion and exclusion criteria.

### Inclusion and exclusion criteria

Inclusion criteria: (1) aged between 60 and 85 years old; (2) living in the community; (3) a smartphone user.

Exclusion criteria: (1) severe neurological disorders (e.g. Alzheimer’s disease, vascular dementia, Parkinson’s disease, history of stroke with significant residual disability), severe psychiatric disorders (e.g. active major depressive disorder, schizophrenia or bipolar disorder), or moderate to severe cognitive dysfunction (MiniMental State Examination score ≤ 20); (2) conditions causing significant motor function impairment (e.g. severe arthritis, spinal cord injury, or muscular dystrophy), or recent fractures or surgeries within the past 6 months that limit mobility; (3) severe speech, language, hearing, or visual impairments that hinder communication with study personnel or participation in the intervention; (4) inability to perform basic activities of daily living independently, as defined by a Barthel Index score ≤ 40 or a Katz Index score ≤ 2; (5) terminal malignant diseases with a life expectancy of less than 6 months; (6) inability or unwillingness to provide informed consent or agree to follow-up.

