### Randomization, blinding, and allocation concealment

Participants who meet the inclusion and exclusion criteria will be randomized into intervention and control groups in a 1:1 ratio. The randomization process will be carried out by a data custodian not involved in the study. The data custodian will generate a set of random numbers using a simple randomization procedure and place into sequentially numbered, sealed, opaque envelopes. The random numbers will be assigned to participants in numerical order. Participants in the intervention group will be informed about the intervention procedure and follow-up plan, while participants in the control group will be informed about the follow-up plan. If participants agree to their assigned plan, they will sign the informed consent and undergo further baseline assessment.

Due to the difficulty of blinding intervention implementers and participants in a multidomain intervention, data collection personnel and statistical analysts will be blinded to reduce bias. Participants are instructed not to disclose their group assignment to anyone during baseline and follow-up assessments.

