### Intervention group

Participants in the intervention group will receive a multidomain intervention including cognitive training, exercise training, and nutritional guidance for a duration of 6 months. The form of the multidomain intervention involves a combination of group and individual interventions. The group intervention sessions will be scheduled biweekly for a total of 12 sessions. Each session will last for 120 min, consisting of 60 min cognitive training, 45 min exercise training, and 15 min nutritional guidance.

After each group intervention session, participants will receive a physical booklet containing the content of the day’s cognitive, exercise, and nutritional intervention, and assignments for the individual family intervention (Supplementary materials). The goals of the individual family intervention include engaging in exercise training, cognitive training, and maintaining a record of healthy eating habits three times a week. Participants will log using the ‘SilverHealth Pro Platform’ app through mobile check-in records (Figure 1).

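### The exclusion list names no cardiac, lung or cardiometabolic contraindication to exercise and has no physician-judgement clause, although it alone decides entry to a largely home-based exercise programme up to age 85.

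*Protocol article*

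**What the plan says.** All references are to the protocol article.

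- **Inclusion and exclusion criteria.** Entry is open to community-dwelling smartphone users aged 60 to 85. Six exclusions follow, several with scale cut-offs (MMSE 20 or below, Barthel 40 or below, Katz 2 or below). The item closest to fitness for exercise is the second: "conditions causing significant motor function impairment (e.g. severe arthritis, spinal cord injury, or muscular dystrophy), or recent fractures or surgeries" in the past 6 months that limit mobility. The list closes with "5) terminal malignant diseases with a life expectancy of less than 6 months; (6) inability or unwillingness to provide informed consent" or to agree to follow-up.
- **Participants and recruitment.** "Physicians from the Fujian Provincial Center for Geriatrics will carry out the screening according to the inclusion and exclusion criteria".
- **Randomization, blinding, and allocation concealment.** "Participants who meet the inclusion and exclusion criteria will be randomized into intervention and control groups in a 1:1 ratio". Those who then accept their assigned plan come to the next step: "they will sign the informed consent and undergo further baseline assessment".
- **Intervention group.** "The group intervention sessions will be scheduled biweekly for a total of 12 sessions". Each session includes 45 min of exercise. "After each group intervention session, participants will receive a physical booklet", which holds the home assignments, and home training is logged in the app.
- **Exercise intervention.** The target is at least three sessions a week, group and home combined, of at least 45 to 60 min. Group sessions cover resistance (made progressively harder with bands, dumbbells and sandbags), balance and flexibility. Aerobic exercise is done at home, and the participant picks the type from a recommended list.
- **Questionnaires.** Medical history, including hypertension and coronary heart disease, is recorded but not linked to eligibility.
- **Safety assessments.** The exercise is described as submaximal and no adverse events are expected. Any that occur are documented and reported within 24 h.

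**The concern.** An eligibility list for an exercise trial in people up to 85 should keep out those for whom the exercise is medically unsafe, either by naming the conditions or by leaving room for a physician's judgement. This list does neither for heart, lung and metabolic disease. The authors plainly considered ability to take part, because they exclude motor impairment, recent mobility-limiting surgery and communication problems that would hinder participation. The cardiorespiratory side is the part left open.

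What is at stake is participant safety. The sample size, power and planned analysis do not depend on it.

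**Working it through.** The plan states no figure on this point, so the check is a reading of the criteria, plus a session count to test whether the programme is mostly home-based.

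**1. What each exclusion covers**

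| Item | Limit covered | Cardiac, lung or cardiometabolic? |
|---|---|---|
| 1 | Severe neurological or psychiatric disease, MMSE 20 or below; includes disabling stroke | No |
| 2 | Motor impairment; recent fracture or surgery limiting mobility | No |
| 3 | Severe speech, language, hearing or visual impairment | No |
| 4 | Dependence in daily living (Barthel 40 or below, or Katz 2 or below) | No |
| 5 | Terminal malignancy | No |
| 6 | Consent or follow-up | No |

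No item gives the physician discretion. Items 1 and 2 do remove some medical limits on exercise: disabling stroke, severe arthritis, spinal cord injury, and recent mobility-limiting fracture or surgery.

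**2. Is this list the operative gate?** Yes. Physicians screen against it, and those who meet it are randomised. The article describes no further medical check between the two.

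**3. Who passes?** A person aged up to 85 with, say, unstable angina or decompensated heart failure passes every item if they walk without significant motor impairment, are independent in daily living, score above 20 on the MMSE, communicate adequately and agree to take part.

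**4. How much exercise is at home?** Inputs are 12 group sessions (Intervention group section) and three sessions a week (Exercise intervention section). Six months is taken as 24 to 26 weeks, and adherence as full; both are assumptions.

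- Sessions in total: 3 × 24 = 72 to 3 × 26 = 78.
- If the three a week include the group session: (72 − 12)/72 = 60/72 = 83%; (78 − 12)/78 = 66/78 = 85%.
- If three home sessions a week are added to the group sessions: 72/(72 + 12) = 72/84 = 86%; 78/(78 + 12) = 78/90 = 87%.
- Range: 83% to 87%. The Discussion gives 10 group sessions instead of 12; on that count the top of the range is 78/(78 + 10) = 78/88 = 89%.
- Group exercise time: 12 × 45 min = 540 min = 9 h over 6 months, with no aerobic training listed in it.

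These shares show where the exercise takes place. They do not measure harm.

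**5. When does each reported safeguard act?**

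| Safeguard | Section | Acts at entry? |
|---|---|---|
| Screening by physicians | Participants and recruitment | Yes, but tied to the listed criteria |
| Physician-led group sessions | Discussion | No |
| Booklet and home assignments issued after group sessions | Intervention group | No |
| Support, rest breaks, adjustment for symptoms, personalised advice | Exercise intervention | No |
| App logging, staff monitoring and feedback | Intervention group; Discussion | No |
| Family help at home | Discussion | No |
| 24 h reporting of adverse events | Safety assessments | No |

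The only safeguard at entry is bound to the list that has the gap. The rest act once a person is already enrolled.

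**The case against.** **An article condenses a fuller protocol, which may hold a clearance step.** The trial has ethics approval and is run by a geriatrics centre whose physicians do the screening. It is therefore fair to say that whether unfit people would actually be enrolled cannot be settled from the article. But the criteria are printed item by item with cut-offs, are not labelled as a selection, and are named as the basis for both screening and randomisation. An eligibility list in that form is not a detail usually left to another document.

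**Physicians would use judgement anyway.** Perhaps, but the article ties screening to the criteria, and undocumented judgement varies between screeners. In this design, consent to the assigned plan follows randomisation. Informal judgement could then be exercised after allocation, when unfitness matters only in the exercise arm.

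**The exercise is submaximal and watched.** This stands in part. The design section says the interventions need close cooperation "under the guidance of healthcare professionals, especially in individual home-based interventions", and the Discussion describes staff following home training through the platform. A reader might infer from the home share that participants exercise unwatched; the article does not support that. These measures lower the risk without closing the gap at entry.

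**Other stronger readings.**

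- That the list names no medical contraindication to exercise at all: items 1 and 2 refute this.
- That gait speed, SPPB, timed up-and-go and sit-to-stand lack cut-offs and should have them: these are outcome measures and would not detect unstable heart or lung disease. A gait-speed cut-off would also remove frail people, whose frailty score is a secondary outcome.
- That the safety section dismisses adverse events: it goes on to require documentation and reporting within 24 h.

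**Conclusion.** The point holds in a limited form. The list covers neurological, psychiatric, motor, orthopaedic and recent-surgery, sensory, dependence and terminal-cancer limits. It leaves out cardiac, lung and cardiometabolic contraindications and gives the screening physician no discretion. No other safeguard in the article fills that gap before randomisation.

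The safety risk per person cannot be derived from the document. The home share of 83% to 87% is context only and rests on 12 group sessions, 24 to 26 weeks and full adherence.

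The change should be made, because it concerns participant safety and is cheap. Confidence is medium, since a fuller protocol may already contain a clearance step. The article does not show that unfit people have been or will be enrolled.

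**What to change.** Add exclusion (7) to the eligibility section: any unstable or severe cardiovascular, pulmonary or metabolic condition that, in the screening physician's documented judgement, makes the trial's exercise programme unsafe. Examples could be unstable angina, decompensated heart failure, uncontrolled arrhythmia or severe uncontrolled hypertension; the investigators should set the final list. Apply it to all candidates before allocation, so that it acts equally on both arms, using the medical history from the questionnaire taken at or before screening. If the full protocol already has such a step, state it in this section.

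The cost is a few more screen failures and a slightly healthier sample, with some loss to the real-world aim. If history is not already taken at screening, that questionnaire moves earlier. The article does not settle this: the Outcome measures section places data collection from the post-randomisation baseline onwards, while Table 1 ticks lifestyle factors, which share the questionnaire with medical history, at screening. If it does move, the ethics committee would need to accept history-taking ahead of the consent signed after allocation, unless an earlier consent step exists.

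Optionally, the safety section could say that risk is expected to be low given this screening and submaximal exercise. That is an editorial change, and the 24 h reporting should stay.
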